**Methods:**

Open-label, multicenter superiority randomized controlled trial in the Netherlands. We will recruit 138 adults (≥ 18 years) with MID or borderline intellectual functioning (intelligence quotient (IQ) 50–85 with adaptive limitations) and hazardous substance use (Alcohol Use Disorders Identification Test (AUDIT) ≤ 19 or Drug Use Disorders Identification Test (DUDIT) ≤ 24; ≥ 12 months) from six intellectual-disability care organizations. Recruitment will be conducted jointly by researchers from Tilburg University and care professionals at the participating organizations. In a Zelen pre-randomization design, eligible clients will be randomized 1:1 to Beat the Kick or CAU using a centralized computer-generated sequence with variable block sizes, stratified by addiction type (alcohol vs cannabis/other drugs). Tilburg researchers will obtain informed consent after allocation (intervention: consent for intervention + assessments; CAU: consent for assessments only). As an open-label trial, only the statistical analyst will remain blinded to allocation via A/B-coded datasets; the allocation key is held by an independent coordinator until primary analyses are complete. Assessments occur at T1 (pre), T2 (post), T3 (1 month), and T4 (6 months). Safety is monitored at T2–T4 through systematic adverse event (AE) and serious adverse event (SAE) recording, and serious events are reported to the Ethics Review Board within 24 h.Primary outcome: autonomous motivation (Treatment Self-Regulation Questionnaire; 15 items; 1–5 scale). Secondary outcomes: substance use ( Substance Use and Misuse in Intellectual Disability Questionnaire (SumID-Q) with AUDIT (0–40; ≥ 8 hazardous; ≥ 20 probable dependence) and DUDIT (0–44; ≥ 6 men/ ≥ 2 women hazardous; ≥ 25 probable dependence)), satisfaction and frustration of psychological needs (Basic Psychological Need Satisfaction and Frustration Scale – Intellectual Disability Version (BPNSFS-ID); 24 items; 1–5), treatment engagement (yes/no), and participant satisfaction. Primary analyses will use intention-to-treat linear mixed-effects models with fixed effects for group, time, and group × time, adjusting for the stratification variable.

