### Strategies to improve adherence to interventions {11c}

Several strategies will be employed to promote adherence to the intervention. A coordinated team, including trainers, supervisors (such as senior practitioners or clinical leads overseeing intervention fidelity), and the primary researcher as the independent monitor, will work together to ensure fidelity and quality. Trainers will be carefully selected from organizations familiar with the intervention’s goals and context. They will meet specific qualifications, including expertise in intellectual disabilities and addiction and, ideally, knowledge of MI. These trainers will receive formal training through RINO Zuid, a Dutch institute specializing in mental health and social care professional development, which includes theoretical instruction, practical exercises, and ongoing supervision to ensure high-quality and consistent delivery of the intervention.

Supervisors will provide regular oversight and feedback to trainers, addressing challenges to maintain fidelity. The independent monitor (primary researcher) will periodically review intervention sessions by analyzing session recordings or attending selected sessions, ensuring adherence to protocols and providing objective feedback to trainers. Trainers will also remain available for participant questions and concerns between sessions, but no additional structured check-ins will be required to maintain feasibility. The intervention will be tailored to align with each participant’s personal goals and needs, ensuring relevance and sustained motivation.

Fidelity will be monitored through detailed documentation, including trainer-completed checklists after each session, and regular reviews by the monitoring team to assess adherence to established protocols. Discrepancies or concerns will be addressed promptly through research team meetings, enabling continuous improvement in adherence strategies.

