In addition, treatment engagement will be captured as initiation of formal SUD treatment (yes/no)—defined as attending ≥ 1 treatment session or completing an intake—within the T3 window (± 1 month post-T2); follow-through on referrals (yes/no) will be recorded separately. Participant-reported acceptability will be assessed at T2 using brief Likert-type items (e.g., clarity, relevance, burden, usefulness, overall satisfaction; 1–5) and open-ended feedback. Safety will be monitored by systematic recording of intervention-related adverse events (AEs) and serious adverse events (SAEs) at T2, T3, and T4 via structured checklists and open queries; definitions, ascertainment procedures, and reporting timelines are detailed in Harms {23}.

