### Adverse event reporting and harms {22}

Adverse events will be closely monitored throughout the study. Harms are defined as any adverse psychological, behavioral, or medical event related to participation, including (but not limited to) increased distress, relapse episodes, psychiatric crisis requiring intervention, or hospitalization.

All reported or observed adverse events will be documented in detail (event, onset/offset, severity, relatedness, expectedness, action taken, outcome), including an assessment of severity and potential relationship to the intervention by the primary researcher. Ascertainment will occur during each study contact (T2, T3, T4) via participant self-report and facilitator observation, with additional spontaneous reporting allowed at any time; relevant chart information will be reviewed where applicable. SAEs will be reported to the Ethics Review Board within 24 h. If necessary, protocol modifications will be implemented promptly to ensure participant safety.

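### The protocol conflicts on whether all adverse events or only related ones are recorded, which puts any comparison of harms between arms at risk of ascertainment bias

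*Protocol article*

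**What the plan says.** **Scope.** Outcomes {12} monitors safety by "systematic recording of intervention-related adverse events (AEs) and serious adverse events (SAEs) at T2, T3, and T4", carried out "via structured checklists and open queries". Adverse event reporting and harms {22} opens with a different filter: "Harms are defined as any adverse psychological, behavioral, or medical event related to participation". Its next paragraph has none: "All reported or observed adverse events will be documented in detail (event, onset/offset, severity, relatedness, expectedness, action taken, outcome"), and this includes an "assessment of severity and potential relationship to the intervention by the primary researcher". The Abstract (Methods) has no relatedness limit either: "Safety is monitored at T2–T4 through systematic adverse event (AE) and serious adverse event (SAE) recording".

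**Source and timing.** The harms section states: "Ascertainment will occur during each study contact (T2, T3, T4) via participant self-report and facilitator observation". It also allows spontaneous reports at any time and chart review where applicable. T2 follows a 10-week period in both arms (Participant timeline {13}).

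**During treatment.** Strategies to improve adherence {11c} provides "trainer-completed checklists after each session", for fidelity, and asks for no further structured check-ins.

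**Thresholds.** Reporting structure (under {21a}) pauses recruitment at two or more related serious events, or when unexpected moderate-to-severe distress occurs in more than 10% of participants.

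**The concern.** Relapse, distress and psychiatric crisis, all named in the harms section, can plausibly occur in either arm. Whether Beat the Kick raises or lowers them can be learned only from a count made the same way in both arms and without a prior judgement of cause. A filter for intervention-related events does not do this, because a CAU participant receives no Beat the Kick and so can hardly have an event attributed to it. The filter also moves the relatedness judgement from a descriptive field to a condition of being recorded, and in this open-label trial the person judging knows the allocation.

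Two further features could make ascertainment unequal or late. Staff who see a participant in ten weekly sessions have many chances to notice an event, and no matching study contact is described for CAU. Structured questioning also begins only once the programme has ended, although Criteria for discontinuing {11b} anticipates distress and deterioration while it is running.

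**Working it through.** The point rests on no stated figure, so there is none to reproduce. The check sets the sections side by side.

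**1. Which events are recorded**

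| Section | Scope |
|---|---|
| Abstract, Methods | All AEs and SAEs |
| Outcomes {12} | Intervention-related |
| Harms {22}, definition | Related to participation (wider than intervention-related) |
| Harms {22}, documentation | All reported or observed, relatedness as a field |

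Site staff cannot follow all four. Outcomes {12} sends the reader to Harms {23} for definitions, but {23} is auditing and harms are under {22}, so the cross-reference as printed does not resolve the conflict.

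**2. Who judges relatedness.** The primary researcher does. Under Implementation {16c} that person generates the sequence and enrols participants, and under {11c} reviews or attends intervention sessions. For this purpose the judgement is not blinded.

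**3. Whether facilitator observation is equal by arm.** The term is not defined.
- Pointing to the intervention arm only: the Discussion uses it for people who could not be blinded, which suggests those delivering the programme, and Statistical methods {20a} assigns trainers exclusively to the intervention group.
- Pointing to both arms: Sequence generation {16a} allows a trainer in either arm, and Trial design {8} describes therapists in both.

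Unequal observation is probable but not established.

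**4. When events are sought.** Structured ascertainment is at T2, T3 and T4. Up to 10 weeks can pass between the first session and the first structured query. In that time detection relies on spontaneous reports and on chart review where applicable. No recall period is given for T2, so it is unclear whether that query covers the treatment weeks.

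**5. What scope does to the distress threshold (illustration).** Inputs: 138 participants, 69 per arm, threshold above 10%, denominator not stated. Assume that only intervention-related distress counts, so that it can arise only among the 69 treated.
- Over 138: 0.10 × 138 = 13.8, so 14 cases are needed; 14/69 = 20.3% of that arm.
- Over 69: 0.10 × 69 = 6.9, so 7 cases are needed; 7/69 = 10.1%.

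The chance of reaching each count, from the binomial upper tail with n = 69 and an assumed true rate in that arm:

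| Assumed rate | At least 14 of 69 | At least 7 of 69 |
|---|---|---|
| 10% | 0.008 | 0.542 |
| 15% | 0.145 | 0.909 |
| 20% | 0.524 | 0.991 |

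The rates are assumptions, and all 69 are taken as enrolled and observed. The scope and the denominator together decide when the rule triggers.

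**The case against.** The strongest reply is that Outcomes {12} defers to the harms section, and that section already documents every event with relatedness as a field. On that reading relatedness is no gate. Participation is also wider than intervention, and CAU clients do participate, through the assessments. In Outcomes {12} the restricting word may apply to the AEs alone, and 24-hour SAE reporting carries no relatedness filter. This stands as far as it goes: the plan does not simply limit recording to related events. It does not remove the conflict, because Outcomes {12} is the section that describes the structured checklists and queries.

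The reply on timing also has weight. Trainers see participants weekly, sessions are reviewed, and an Independent Safety Auditor checks the event logs at least quarterly and may assess relatedness when required. With recruitment planned from July 2025 to June 2026, early participants' T2 data would arrive while later ones are in treatment. The trial is described as minimal-risk, so the frequency of questioning is partly a matter of proportion. Even so, an audit of logs cannot show events that nobody asked about.

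A reader might infer three stronger things:
- *That CAU events are near zero by definition.* This follows only if Outcomes {12} overrides the harms section.
- *That facilitators exist only in the Beat the Kick arm.* This is an inference from {20a} and the Discussion, and {8} and {16a} point the other way.
- *That the arms cannot be compared on harm.* Checklists, open queries, self-report and chart review are not restricted to one arm, and substance use is measured at T1–T4 without any relatedness judgement. The protocol also promises no between-arm test of harms.

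**Conclusion.** The concern holds as a contradiction on scope, with a risk of ascertainment bias attached. It is not a demonstration that harms are unmeasurable. The sections give incompatible rules. If a relatedness filter is applied, an unblinded judgement decides which events count, and it cannot be applied equally in CAU. Facilitator observation probably adds to the imbalance, and no structured query falls within the 10 treatment weeks.

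The size of the bias cannot be computed, because the documents give no event rates by arm. The only figures available concern the pause threshold: 14 or 7 cases, depending on the denominator, if related distress alone counts. The conclusion assumes that staff might follow Outcomes {12} as written. If the documentation rule in the harms section governs throughout, what remains is the undefined observer, the gap before T2 and the wording to be reconciled. The change is worth making either way, since it is cheap and its benefit does not depend on which reading was intended.

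**What to change.** - Delete 'intervention-related' in Outcomes {12} and 'related to participation' in the harms definition, so that all AEs and SAEs are recorded in both arms with relatedness as a field.
- Base any between-arm summary only on the T2–T4 checklist and open queries, given identically in both arms, and state that the T2 query covers the whole treatment period.
- Define facilitator, and list facilitator- or trainer-observed events separately.
- Add an adverse-event line to the existing trainer session checklist, for safety monitoring only. It would increase detection in the intervention arm alone, so it must stay out of the comparison.
- Reconcile Outcomes {12}, Reporting structure and Harms {22}. State the denominator of the 10% threshold, and correct the cross-reference from Harms {23} to {22}. No threshold needs to change for this.

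The cost is some rewording and one form line. The downside is more events to log, many of them background events unrelated to the programme.

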### Participant timeline {13}

Participants will be enrolled in the study following a thorough screening and informed consent process. The intervention period will last 10 weeks, during which participants will receive either the Beat the Kick intervention or CAU support. Assessments will be conducted at four key time points: pre-treatment (T1), post-treatment (T2), and during follow-ups at 1 month (T3) and 6 months (T4). This structured timeline ensures a comprehensive evaluation of both the immediate and long-term effects of the intervention. A schematic diagram of participant flow is presented in Fig. 2, and the detailed schedule of enrolment, interventions, and assessments is shown in Fig. 3.

**Fig. 2 Fig2:**
[figure not shown]
Consort diagram

**Fig. 3 Fig3:**
[figure not shown]
SPIRIT schedule of enrolment, interventions, and assessments

### Sample size {14}

A sample size power analysis was performed using G*Power 3.1.9.7 [36] to ensure the study’s feasibility within its constraints and the available population of individuals with mild intellectual disabilities (MID) who abuse substances. The calculation was based on the primary hypothesis, which posits that participants receiving the Beat the Kick intervention will show greater improvement in autonomous motivation compared to those in the control group. The analysis assumed a between-group design with four measurement points: pre-treatment (T1), post-treatment (T2), and follow-ups at 1 month (T3) and 6 months (T4). An effect size of *f* = 0.25 (medium effect), a power of 80%, and a significance level of 5% (two-sided) were used, with default settings for the correlation among repeated measures (0.5) and the non-sphericity correction (ε = 1, assuming sphericity).

The power analysis indicated that a sample of 82 participants is required to detect the expected effect with 80% power. Given the elevated risk of dropout among individuals with MID and co-occurring substance use—estimated at approximately 40% based on previous studies—the recruitment target was increased to 138 participants.

This adjusted target accounts for anticipated attrition and ensures that a sufficient number of participants will complete the study to maintain statistical power. Although recruiting 138 individuals from this population poses logistical challenges, it is considered feasible through targeted recruitment strategies, including partnerships with care providers and the use of established professional networks. This adjusted recruitment plan acknowledges the inherent risks of higher dropout rates but ensures the robustness of the study’s findings and feasibility within its framework.

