### Outcomes {12}

The primary outcome is the change in autonomous motivation for substance-abuse treatment, measured using an adapted version of the TSRQ [21]. The TSRQ comprises 15 items rated on a 5-point Likert scale (1 = completely untrue; 5 = completely true). Subscales are scored as means (range 1–5) and include autonomous motivation (internal consistency α≈0.84; primary endpoint), controlled motivation (α≈0.78), and amotivation (α≈0.41; analyzed exploratorily due to lower reliability). As participation in the intervention and any subsequent treatment is voluntary, baseline motivation may be relatively high; this will be considered when interpreting change. Assessments will occur at pre-treatment (T1), post-treatment (T2), and follow-ups at 1 month (T3) and 6 months (T4), with the primary endpoint defined as Δ(T2–T1) on autonomous motivation and maintenance examined at T3/T4. To optimize comprehension for MID/BIF participants, all self-reports will be interviewer-assisted.

Secondary outcomes include reductions in substance use and related problems, measured with the SumID-Q (patterns, frequency, consequences), which embeds the AUDIT and DUDIT screens. The AUDIT has 10 items (item scores 0–4; total 0–40) with commonly used cut-offs ≥ 8 for hazardous use and ≥ 20 for probable dependence. The DUDIT has 11 items (item scores 0–4; total 0–44) with cut-offs for hazardous use of ≥ 6 for men and ≥ 2 for women, and ≥ 25 for probable dependence. Both continuous totals and categorical classifications (none/hazardous/probable dependence) will be analyzed at T1, T2, T3, and T4 (recall periods per instrument guidance). Psychological need satisfaction and frustration will be assessed with the Basic Psychological Needs Satisfaction and Frustration Scale – Intellectual Disabilities (BPNSFS-ID; 24 items, 5-point Likert), yielding mean scores (range 1–5) for autonomy, competence, and relatedness (higher satisfaction = greater fulfillment; higher frustration = greater need thwarting) at T1, T2, T3, and T4 [35].

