## Statistical methods

### Statistical methods for primary and secondary outcomes {20a}

Data analysis will be conducted using R version 4.5.0 or later [41], following standard procedures for descriptive and inferential analyses.

The primary objective of this RCT is to assess the effectiveness of the Beat the Kick intervention compared to CAU in enhancing autonomous motivation for substance abuse treatment among adults with MID. It is hypothesized that participants in the Beat the Kick group will exhibit greater improvement in autonomous motivation from pre-test to post-test compared to the CAU group, with an anticipated medium effect size.

Linear mixed models (LMM) will be employed to test this primary hypothesis using the lme4 package in R [42]. LMMs are particularly suited for repeated measures data, accommodating both fixed and random effects [42]. Models will include fixed effects for group (Beat the Kick vs CAU), time (T1–T4), and the group × time interaction (primary effect of interest), with random intercepts and random slopes for time at the participant level to capture individual trajectories. The randomization stratification variable “addiction type” (alcohol vs cannabis/other drugs) will be included as a fixed effect in all models to adjust for baseline heterogeneity between strata; exploratory interaction terms with group and time (e.g., group × time × addiction type) will be examined to assess effect modification [43]. Baseline outcome values will serve as covariates to control for initial differences, mitigating regression to the mean [44].

Analyses will primarily adhere to the intention-to-treat (ITT) principle, preserving the integrity of randomization and providing a conservative estimate of the intervention’s effectiveness [45]. This approach ensures that all participants are analyzed in their originally assigned groups, irrespective of adherence or dropout. Complementary per-protocol (PP) analyses will also be conducted for participants who completed the intervention as intended, providing additional insights. Missing data will be handled using maximum likelihood estimation, a robust method that assumes data are missing at random, leveraging all available information without requiring imputation [46].

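### The 82-participant calculation powers the arm difference averaged over T1–T4, not the T1-to-T2 primary endpoint; with 82 at T2, the baseline-adjusted contrast has about 73% power

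*Protocol article*

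**What the plan says.** Sample size {14} ties the calculation to the primary hypothesis: "The calculation was based on the primary hypothesis, which posits that participants receiving the Beat the Kick intervention will show greater improvement in autonomous motivation". It then describes the test: "The analysis assumed a between-group design with four measurement points", namely T1, T2, T3 and T4. The inputs are f = "0.25 (medium effect"), "a power of 80%, and a significance level of 5% (two-sided) were used", and "default settings for the correlation among repeated measures (0.5"), with sphericity assumed. The result is stated as "The power analysis indicated that a sample of 82 participants is required to detect the expected effect with 80% power". An expected dropout of about 40% raises this to 138.

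Outcomes {12} fixes the endpoint as a change between two visits, "with the primary endpoint defined as Δ(T2–T1) on autonomous motivation and maintenance examined at T3/T4". The primary objective in Objectives {7} words the hypothesis the same way, as greater improvement from pre-test to post-test. Statistical methods {20a} repeats that hypothesis, attaches a medium effect size to it, and specifies a mixed model with fixed effects for group, "time (T1–T4), and the group × time interaction (primary effect of interest"). The same section plans to adjust for the baseline value of the outcome.

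**The concern.** A between-group test on four measurements asks whether the arms differ on average over all four visits. It contains no change component. The hypothesis that the section says it is powering is about change, and the endpoint uses only T1 and T2.

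Averaging four correlated measurements makes the comparison more precise than one at T2 alone. It also counts T1, where no treatment effect can be expected. So 80% power for the averaged comparison does not carry over to the T1-to-T2 contrast.

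This is the protocol's only power justification. If it stands, a null primary result could be read against 80% power that was calculated for a different quantity.

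**Working it through.** **Inputs from Sample size {14}:** f = 0.25, two groups, m = 4 measurements, correlation r = 0.5, two-sided 5%, 80% power, 82 evaluable, about 40% dropout, 138 recruited. For two equal groups f = 0.25 corresponds to d = 2 × 0.25 = 0.5.

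**1. Reproducing 82.** For the repeated-measures between-factors test, the noncentrality is λ = f²·N·m / [1 + (m − 1)r], with 1 and N − 2 degrees of freedom.
- N = 82: λ = 0.0625 × 82 × 4 / 2.5 = 8.2; power 0.808.
- N = 80: λ = 8.0; power 0.798.

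So 82 is the smallest even N that reaches 80%. Other options do not give it: the group-by-time interaction gives 24 (four measurements) or 34 (two), the between-factors test with two measurements gives 98, and a two-sample t-test at d = 0.5 gives 128.

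**2. Reproducing 138.** 82 / (1 − 0.4) = 136.7, so 137, or 138 as an even number for 1:1 allocation. Both stated figures follow from their inputs. The fault is the contrast, not the arithmetic.

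**3. Power for T1 to T2 with 82 at T2 (41 per arm).** Take d = 0.5 at T2 and r = 0.5, in units of the outcome SD, and use the noncentral t.
- Baseline-adjusted: residual SD = √(1 − r²) = √0.75 = 0.866; ncp = (0.5 / 0.866) × √(41/2) = 2.61; power 0.733. Detectable difference at 80% power: about 0.54 SD.
- Unadjusted change: SD = √[2(1 − r)] = 1; ncp = 0.5 × √(41/2) = 2.26; power 0.609.

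**4. Numbers with T2 data needed for 80%.** Adjusted: 98 (49 per arm, power 0.81). Change score: 128 (64 per arm).

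**5. Dependence on loss by T2 (d = 0.5, r = 0.5).**

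| With T2 data | Loss from 138 | Adjusted | Change score |
|---|---|---|---|
| 82 | 41% | 73% | 61% |
| 98 | 29% | 81% | 69% |
| 110 | 20% | 85% | 74% |
| 138 | 0% | 92% | 83% |

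The break-even loss for the adjusted contrast is 1 − 98/138 = 29%. The protocol gives no dropout by visit, so the rows from 98 upward are illustrations.

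**6. Dependence on r (82 at T2).** Adjusted / change score: 65% / 47% at r = 0.3; 73% / 61% at 0.5; 80% / 71% at 0.6; 88% / 82% at 0.7. The plan's 0.5 is a software default, so the other values are assumptions that show the range.

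**7. The test actually used, under a plausible pattern.** If the arms differ by 0 at T1 and by 0.5 SD at T2, T3 and T4, the averaged difference is (0 + 3 × 0.5)/4 = 0.375 SD. The between-factors test with 82 then has 56% power.

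**The case against.** **The 73% and 61% are conditional.** They hold if only 82 people have T2 data. The protocol applies its 40% to completing the study, which runs to the six-month follow-up, whereas T2 follows a 10-week intervention period. The maximum-likelihood mixed model uses all available observations, so someone lost after T2 still contributes to the primary contrast. This stands. A reader might infer that the trial as planned lacks 80% power for its primary endpoint; the protocol does not support that, because the loss by T2 is not given and adjusted power is adequate up to about 29% loss.

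**The 61% is not the planned analysis.** Baseline adjustment is specified, so 73% is the relevant figure and the change-score figure is a secondary bound. This also stands.

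**The between-factors test need not assume a difference at T1.** A reader might infer that it requires the arms to differ by 0.5 SD already at baseline. It requires 0.5 SD on average over the four visits. A difference of 0 at T1 and 0.667 SD at T2 to T4 satisfies that equally, and 82 at T2 would then give 93% (adjusted) or 85% (change). The protocol never states such a pattern, however, and Statistical methods {20a} attaches the medium effect to pre-to-post improvement, so 0.5 SD at T2 is the more natural reading.

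**The model is not purely a T1-to-T2 comparison.** The primary effect named there is the group-by-time interaction over T1 to T4. That is correct, but the averaged group difference matches neither that interaction nor the T1-to-T2 endpoint.

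**Trainer clustering.** The plan models trainer as a random effect and the sample size makes no allowance for it. No intraclass correlation or number of trainers is given, and the text is unclear on whether trainers exist in one arm or both: Sequence generation {16a} assigns them to either arm, Statistical methods {20a} to the intervention only. The direction is clear; the size is not a finding.

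**Conclusion.** The claim that 82 participants give 80% power for the primary hypothesis is wrong as written. The figure belongs to the arm difference in the T1–T4 mean. For the planned baseline-adjusted T1-to-T2 contrast, 82 participants with T2 data give about 73%, seven points below the stated level, and 98 would be needed.

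The size of the gap rests on three assumptions: that the medium effect means 0.5 SD at T2, that r is 0.5, and that the whole 40% is lost by T2. Changing them changes or removes the shortfall; it does not make the calculation one for the primary endpoint. The type I error rate and the treatment estimate are unaffected.

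**What to change.** Keep the target of 138. Replace the power statement with one for the baseline-adjusted difference at T2, for example: with a difference of 0.5 SD, a T1–T2 correlation of 0.5 and a two-sided 5% level, power is 73% with 82 participants at T2 (detectable difference about 0.54 SD), 81% with 98, 85% with 110 and 92% with 138.

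State what share of the 40% dropout is expected by T2, and that adjusted power stays at or above 80% up to about 29% loss by then. Because r = 0.5 is a default, show the range over r as well.

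Add a separate caveat that the trainer clustering the plan models would lower these figures. Any intraclass correlation, number of trainers and choice of clustered arm should be labelled as assumptions.

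The cost is one rewritten paragraph and possibly a less favourable stated power. No extra participants are needed, and the design and primary model do not change.
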